### Sample size

A total sample size of 30 participants was calculated as required to detect a change in 4 mmHg in SBP with the proposed crossover design, using an estimated within-participant standard deviation of 5.45 mmHg and a power of 0.80 and *α* = 0.05 [13]. A recruitment goal of 35 participants has been set to account for the potential participant drop out.

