### Study groups

Eligible participants will be assigned randomly to one of the following sequences: ABC, ACB, BAC, BCA, CAB or CBA. So, all the participants will be provided with all three treatments in a crossover design.

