### Statistical analysis

Statistical analysis will be performed in an intent-to-treat fashion. In addition, a per-protocol analysis will also be performed to check for potential effect attenuation due to unequal compliance or protocol deviations across treatments. Statistical analysis will be performed using SAS 9.4. The endpoint of treatments and baselines will be compared using a mixed-model analysis of variance. Sequence and sex will be included as fixed factors, and participant will be included as a random factor, with participant repeated by period.

Dunnett’s test will be used to adjust for multiple comparisons with the endpoint of the baselines set as the control. Effects of treatment by time on measures repeated during treatments will be assessed using a mixed-model analysis of variance with sequence, sex, time as fixed factors and participants included as random factors, with participants repeated by period, with Tukey-Kramer adjustments for multiple comparisons. Model residuals will be visually inspected to assess independence, normal distribution, and constant variance. Datasets with residuals determined to violate these assumptions will be transformed prior to re-analysis. Results will be expressed as estimated least square means ± standard error of the mean (SEM) for all values. Statistical significance will be set at *p* < 0.05 for all analyses.

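### The 80% power for 4 mmHg assumes one unadjusted contrast; for the Dunnett-adjusted comparisons with baseline (Hypothesis 1) it is about 67% per comparison

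*Protocol article*

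**What the plan says.** The Sample size section states: "A total sample size of 30 participants was calculated as required to detect a change in 4 mmHg in SBP". The inputs follow in the same sentence: "using an estimated within-participant standard deviation of 5.45 mmHg" and "a power of 0.80 and *α* = 0.05". The section names neither a contrast nor a multiplicity adjustment. It then adds: "A recruitment goal of 35 participants has been set to account for the potential participant drop out".

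The Objectives and hypothesis section sets three hypotheses, all on 24-h SBP:
- Hypothesis 1: each of casein, HSP and HSP+ against baseline.
- Hypothesis 2: the hemp treatments against casein.
- Hypothesis 3: HSP+ against HSP.

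Under Outcomes and measurement tools, 24-h SBP is the primary outcome. It is measured once at the start of the first phase and once near the end of each phase.

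The Statistical analysis section says that Dunnett's test "will be used to adjust for multiple comparisons with the endpoint of the baselines set as the control". It attaches the Tukey-Kramer adjustment to a separate treatment-by-time model for measures taken repeatedly within a treatment period. The significance threshold is general: "Statistical significance will be set at *p* < 0.05 for all analyses".

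**The concern.** The sample size and the test for Hypothesis 1 are both fixed in the article, and they do not match. The sample size rests on one comparison tested at the full 5% level. Hypothesis 1 consists of three comparisons with a shared baseline, and Dunnett's test holds the error rate across all three by using a larger critical value. The same 30 participants therefore have less power for each of these comparisons than the only power figure the article gives.

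What is at stake is how a non-significant result is read. If one of the proteins does not differ significantly from baseline, a reader who relies on the stated 80% will take the risk of having missed a true 4 mmHg fall to be 20%. Under the planned test it is about 33%.

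**Working it through.** **Inputs.** From the Sample size section: n = 30, difference 4 mmHg, within-participant SD 5.45 mmHg, power 0.80, alpha 0.05. From Study groups: "all the participants will be provided with all three treatments in a crossover design". From Objectives and hypothesis and Statistical analysis: three comparisons with baseline under Dunnett's test. Sidedness is not stated, so two-sided is assumed.

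**1. Reproduce the plan's figure.** In a crossover each participant contributes to both sides of a contrast, so

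n = 2 × [SD × (z₀.₉₇₅ + z₀.₈₀) / difference]² = 2 × [5.45 × (1.960 + 0.842) / 4]² = 29.1, rounded up to 30.

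Other readings do not give 30:

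| Reading | n |
|---|---|
| One-sided test | 23 |
| 5.45 taken as the SD of the paired difference | 15 |
| Bonferroni for 2, 3 or 6 tests | 36, 39 or 45 |

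**2. Power of that unadjusted contrast at n = 30.**

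SE = 5.45 × √(2/30) = 1.407 mmHg; non-centrality = 4 / 1.407 = 2.843.

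For a contrast among the three treatments, residual df = 2 × 29 − 2 = 56 and the critical value is 2.003. Non-central t power is 0.798, in line with the stated 0.80.

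**3. Power under Dunnett's test.** There are four conditions, baseline and three treatment endpoints, so df = 3 × 29 = 87. With three comparisons against a shared control (correlation 0.5), the two-sided 5% critical value is about 2.39. SE and non-centrality are as in step 2.

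| Completers | SE (mmHg) | Non-centrality for 4 mmHg | Critical value | Power per comparison |
|---|---|---|---|---|
| 30 | 1.407 | 2.843 | 2.39 | 0.67 |
| 35 | 1.303 | 3.070 | 2.38 | 0.75 |
| 39 | 1.234 | 3.241 | 2.38 | 0.80 |

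**4. Difference detectable with 80% power at n = 30.** Solving the non-central t for power 0.80 with critical value 2.39 and df 87 gives 4.56 mmHg. The approximation (2.39 + 0.84) × 1.407 = 4.54 agrees closely.

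**5. Sensitivity to method.** The normal approximation gives 0.81 unadjusted and 0.69 with Dunnett's test. The gap of about 12 percentage points does not depend on the degrees of freedom chosen.

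**The case against.** **The arithmetic is correct, and sizing on one contrast is common practice.** This stands. The 30 reproduces, and the section does not claim that its 80% allows for multiplicity. The fault is a mismatch between the planning figure and one of the planned tests, not a miscalculation.

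**The 80% may refer to a comparison between treatments.** This stands too. The Statistical analysis section does not clearly assign an adjustment to Hypothesis 2 or 3 on 24-h SBP, and a single unadjusted pairwise contrast there keeps about 0.80. But the article does not say that this is the contrast meant, and on that reading it gives no power figure for Hypothesis 1, the first it lists.

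**A reader might infer that every planned test falls short, because Tukey-Kramer is also mentioned.** The document does not support this. It ties Tukey-Kramer to measures repeated within a treatment period, such as office blood pressure with its midpoint reading. 24-h SBP is taken once per phase, so no Tukey-Kramer loss of power can be charged to the primary outcome.

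**The 67% is only one definition of power.** True: it is the chance that one pre-named comparison succeeds. If all three treatments truly lower 24-h SBP by 4 mmHg, simulation with a shared baseline and the same SD and df gives about 0.88 for at least one success and about 0.44 for all three. Hypothesis 1 speaks of protein of any type, so the restated figure should be labelled as per comparison.

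**The detail may be in the full protocol or analysis plan.** It may, but both the sample size and the Dunnett adjustment are stated here, and the discrepancy follows from those two statements alone.

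**Conclusion.** The point holds for Hypothesis 1. With 30 completers, each Dunnett-adjusted comparison with baseline has about 67% power for 4 mmHg, not 80%. The difference detectable with 80% power is about 4.6 mmHg. The margin for dropout does not close the gap: power is about 75% even if all 35 complete, and about 39 completers would be needed.

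It does not follow that the trial as a whole has 67% power, or that the 80% is wrong for a single unadjusted contrast between two treatments.

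The result assumes a two-sided test, 5.45 mmHg as the within-participant SD for baseline and treatment values alike, complete data, and a true 4 mmHg difference in the comparison tested. The two-sided and SD readings are the ones that reproduce 30. The trial is not invalidated, but its only stated power figure does not apply to the first hypothesis as it will be tested.

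**What to change.** In the Sample size section, name the contrast to which the 4 mmHg and the 80% refer. Then add a sentence such as: for the Dunnett-adjusted comparisons of each treatment with baseline, 30 completers give about 67% power per comparison for a 4 mmHg difference, or 80% power for about 4.6 mmHg.

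Neither enrolment nor the planned tests change. The only cost is a less favourable stated figure for Hypothesis 1.

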### Study setting

This study will be conducted at one site the RCFFN, University of Manitoba, Winnipeg, Manitoba, Canada [name] (Winnipeg is the capital and largest city of the province of Manitoba, with a population of approximately 775,000 people, of primary European decent, but with a significant Indigenous and Filipino population). The site investigator is [name] at the RCFFN, University of Manitoba.

### Study population

Thirty-five participants will be enrolled into the study using advertisements in local media including social media, newspapers and the official website of the Richardson Centre and on University Campuses, as well as our pre-existing database of participants. Potential participants will be initially screened over the telephone using a telephone questionnaire where some brief questions regarding personal health information will be asked. If participants are determined as potentially eligible after telephone screening, they will be scheduled to come to the RCFFN in the morning to have their BP measured and undergo a blood screening where 20 ml fasting blood samples will be taken via venipuncture by a nurse in order to test for blood parameters related to the exclusion criteria. If the potential participants meet all the inclusion criteria before they go for the blood draw and not the exclusion criteria, the informed consent form will be provided by the study coordinator and the participant will sign the form and will be recruited to the study.

### Inclusion criteria

Hypertensive participants aged 18–75 years will be recruited, with a Body Mass Index (BMI) between 18.5 and 40 kg/m^2^. Participants must have a SBP between 130 and 160 mmHg and a DBP ≤ 110 mmHg. Additionally, participants must be willing to fast for 10–12 h and abstain from alcohol for 2 days prior to blood sampling and BP measurement. They must also abstain from coffee consumption for at least 14 h and physical exercise for at least 4 h before BP measurement. All women of child-bearing age will take a pregnancy test prior to commencement of the trial. The pregnancy test should be negative for women with child-bearing potential. All participants must be able and willing to give informed consent to participate in the trial prior to their inclusion.

### Exclusion criteria

Participants will be excluded if they are undergoing change in, or have changed, the type or dosage of anti-hypertensive drug treatment, regular high-dose non-steroidal anti-inflammatory drug (NSAID) treatment, cyclosporine or tacrolimus in their treatment for less than 3 months. Participants will be excluded if they have any dietary restrictions, which would prevent them from consuming the trial treatments. Participants must not have self-reported weight gain or loss greater than 5 kg in the past 3 months. Participants must be free of active cardiovascular disease including stroke, congestive heart failure, myocardial infarction, unstable angina pectoris, coronary artery bypass graft, percutaneous transluminal coronary angioplasty, temporal ischemic attacks, anemia, abnormal electrolytes, proteinuria, abnormal liver, kidney, thyroid function, bleeding/blood or psychiatric disorder. There will be some exceptions regarding some medications/supplements consumption by the participants. Those participants taking BP medications who have been stable on the medication for at least 3 months will be included in the study. Those taking medications (i.e., statins) or supplements (i.e., fish oils) for lipid lowering reasons and have been stable on such medications and supplements for at least 3 months will be included in the study. Participants with stabilized thyroid levels with treatment will be allowed to participate in the study.

Participants will be asked about current or historical diseases/conditions through verbal question and answer during screening. Participants will be excluded if they have clinically significant biochemistry defined as: sodium < 134 mmol/l, > 148 mmol/l; fasting glucose > 6.1 mmol/ l or any other clinically significant abnormality in hematology and/or biochemistry at the investigator’s discretion.

Participants will be excluded if they have secondary hypertension, have type 1 or type 2 diabetes, a history of cancer or malignancy in the last 5 years, or any metabolic disease, gastrointestinal disorder or other clinically significant disease/disorder, which could interfere with the results of the study or the safety of the participant or those with allergies or sensitivities to any of the ingredients in the study product.

Participants will be excluded if they smoke tobacco, use snuff, are nicotine users, recreational drug users, or if they consume more than 14 alcoholic beverages a week. Women with child-bearing potential not using an acceptable method of birth control (i.e., implants, injectables, combined oral contraceptives, some intrauterine contraceptive devices (IUDs), sexual abstinence or a vasectomized partner) or who are pregnant or plan to become pregnant during the trial period or women who are breastfeeding will be excluded.

### Conditions for withdrawal from the trial

The following criteria are to be considered sufficient reason for discontinuing participation in the trial: non-compliance by the participant; developing condition(s) or consumption of supplements or medications as specified under the exclusion criteria or changing the type or dosage of the specified medications; presenting an adverse event or any other medical situation where, in the opinion of the qualified investigator, continuation of the trial treatment would compromise the participant’s health; abusive behavior of a participant towards trial staff; participant’s withdrawal of consent and self-removal from the trial for any reason. We will follow up with study participants who have been withdrawn from the trial due to an adverse event, until symptoms have resolved.

### Randomization and concealment procedures

Recruited eligible participants will be randomly assigned to one of the treatment sequences using a 3 × 3 Latin-square design. The letters A, B and C represent the three treatment groups and the sequences are as follows: ABC, ACB, BAC, BCA, CAB and CBA. The randomization procedure will be completed using a random-number generator.

### Blinding

Due to the fact that the casein powder, HSP and HSP+ have different visual appearances, treatment smoothies will be prepared by a kitchen staff member to reduce the differences in treatment appearance and given to the clinical coordinators in a blinded fashion labeled A, B or C. Assignment of treatments to labels will be performed by a researcher independent of the investigators’ groups. This researcher will keep a copy of the treatment coding, give a copy of the treatment coding to the assigned kitchen staff, and give a sealed copy of the coding to the principal investigator allowing participants, coordinators and individuals performing the analyses and collecting outcome data to be blinded to the treatments. Participants will be instructed not to communicate about the taste and texture of the smoothies with the research staff or other participants in an attempt to ensure double-blinding. The treatment coding will be broken after the conclusion of the statistical data analyses on the primary outcome. However, the code could be broken if there is an adverse event reported which requires identification of the treatment.

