**Fig. 2 Fig2:**
[figure not shown]
Representation of the trial enrollment, interventions and analysis

During each treatment period, participants need to come to the RCFFN twice a week on Tuesdays and Fridays to consume one treatment under supervision and pick up treatments for the next 2 or 3 days. Each treatment consists of a frozen fruit smoothie (mango or pineapple), fruit juice (diet mango juice), sorbet and 25 g of protein from treatment-protein powder and the treatments will be consumed twice a day. HSP and the HSP+ powder has a green color and a stronger taste than casein-protein powder; however, our team has identified that by using a combination of frozen fruit and sorbet in the fruit smoothies this color and taste can be well-masked.

Participants will be instructed to consume two or less alcoholic beverages and no more than three 8-oz. cups of caffeine-containing beverages per day during the trial period. Participants will be instructed to perform their normal daily activities during the measurement day. Prolonged intense physical activity will be discouraged on measurement days and the days preceding measurement days. Participants will be strongly recommended to maintain consistency in their physical activities and dietary pattern during the trial period. A 3-day food record will be collected during the first day of the first phase and during the final week of each treatment period to be analyzed for calorie intake during the study.

During the study period, body weight will be monitored as a change could occur due to the inclusion of extra protein in a free-living condition. All outcome variables will be adjusted for changes in body weight should significant changes occur between treatments. Gastrointestinal tolerability and weekly monitoring questionnaires will be completed by participants weekly during each intervention period.

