### Outcomes and measurement tools

The primary outcome of this trial will be 24-h SBP, measured at the first day of the first phase and day 41 of each treatment phase using ambulatory BP monitors (ABPM, OnTrak, Spacelabs Healthcare Inc., Snoqualmie, WA, USA) [50, 51]. Participants will be fitted with an ABPM to wear for a full day. Continuous and SBP and DBP measured over 24 h will be recorded.

Office-measured BP, pulse-wave velocity and augmentation index will be determined using an automated oscillometric measurement device (Mobil-O-Graph, IEM, Stolberg, Germany) in an office setting at days 1 and 41 of each treatment phase [52, 53]. Office-measured BP will also be measured at day 22 to track the changes at the midpoint of each treatment phase. This measurement will take place in a quiet room while the participant is in a seated position with their arm resting on an arm rest at heart level. Participants will be advised to rest quietly throughout the measurements. Oscillometric measurement will be performed four times at 2-min intervals. The first measurement will be discarded, and the last three measurements will be averaged to determine office-measured BP. The LCD display of the oscillometric measurement device will be covered so that the participant is blinded to the BP values during the measurements. BP results will not be shared with participants until they have completed the trial.

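### The treatment code is opened once 24-h SBP has been analysed, so the protocol allows about 40 other outcomes to be analysed with treatments known

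*Protocol article*

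**What the plan says.** The Blinding section of the protocol article has treatments labelled A, B and C and the key held by an independent researcher, the kitchen staff and, sealed, the principal investigator. The stated purpose is "allowing participants, coordinators and individuals performing the analyses and collecting outcome data to be blinded to the treatments". That promise is not limited to one outcome. The section then gives it an end point: "The treatment coding will be broken after the conclusion of the statistical data analyses on the primary outcome". The only other route is the safety exception: "However, the code could be broken if there is an adverse event reported which requires identification of the treatment".

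Outcomes and measurement tools names one primary outcome: "The primary outcome of this trial will be 24-h SBP, measured at the first day of the first phase and day 41 of each treatment". That section and the three that follow it (anthropometric, blood and urine measurements) list all the other variables.

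Statistical analysis has model residuals judged by eye, and then: "Datasets with residuals determined to violate these assumptions will be transformed prior to re-analysis". The section names neither a criterion nor a transformation.

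Sample collection has blood and urine frozen until they are analysed, and Availability of data says the same. Neither places the assays before or after the code is opened.

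**The concern.** The blinding of analysts and outcome assessors is promised in general terms, but the stated end point secures it for one variable only. From then on, anyone working on the remaining outcomes may know which treatment each label stands for.

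This matters because some judgement remains to be exercised. Whether residuals look acceptable, and which transformation to use if they do not, is decided dataset by dataset, and re-analysis implies that an untransformed fit has already been seen. Anticipated results and conclusion states in advance that blood NO should rise on the hemp treatments and that ACE activity should fall most on HSP+ (hemp seed protein plus hydrolysate), and these results are to support the account of mechanism. A subjective choice, a declared expected direction and knowledge of treatment could therefore coincide on the outcomes meant to explain any blood pressure effect.

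**Working it through.** The plan gives no figure on this point, so the check is a count of what the primary-only trigger leaves out and an ordering of events around the code break.

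**Step 1. Count of variables other than 24-h SBP** (food records and tolerability questionnaires not counted)

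| Source section | Variables | Number |
|---|---|---|
| Outcomes and measurement tools | 24-h DBP ("Continuous and SBP and DBP measured over 24 h will be recorded") | 1 |
| Outcomes and measurement tools | office SBP, office DBP, pulse-wave velocity, augmentation index ("Office-measured BP, pulse-wave velocity and augmentation index will be determined using an automated oscillometric measurement device") | 4 |
| Anthropometric measurements | weight, waist, hip | 3 |
| Anthropometric measurements | DXA fat and lean mass | 2 |
| Blood biochemical measurements | 4 lipids, glucose, creatinine, BUN, AST, ALT, GGT, total protein, albumin | 12 |
| Blood biochemical measurements | insulin and 2 HOMA indices | 3 |
| Blood biochemical measurements | ACE activity, angiotensin II, aldosterone, renin, epinephrine, norepinephrine, NO | 7 |
| Urine biochemical measurements | 6 analyzer measures, NO, epinephrine, norepinephrine | 9 |

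Total: 1 + 4 + 3 + 2 + 12 + 3 + 7 + 9 = 41. Of these, 12 + 3 + 7 + 9 = 31 come from stored blood or urine.

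**Step 2. Order of events**

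- Before the break: ambulatory and office pressures, vascular measures, anthropometrics and DXA are all recorded during the treatment periods. Their collection is not exposed; only their analysis can be.
- Before the break: the comparison of body weight between treatments. Study design says "All outcome variables will be adjusted for changes in body weight should significant changes occur between treatments", and the Discussion names BP among those outcomes. The rule thus covers 24-h SBP, whose analysis cannot conclude until the weight question is settled. Taking body weight off the list leaves 41 − 1 = 40.
- Not placed in time: the assays of stored samples, and the residual and transformation decisions for the other 40 variables. The text lets all of these follow the break.

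**Step 3. How much room one open choice gives (illustration only)**

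Assumptions, not taken from the protocol: log-normal data, no treatment effect, one paired comparison, and between- and within-participant log-scale SDs each equal to 0.7 × s. The number of participants is 30, from Sample size. With 20,000 simulated trials per setting, the rejection rates at p < 0.05 are:

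| s | raw scale only | log scale only | better of the two |
|---|---|---|---|
| 0.3 | 4.8% | 4.9% | 5.95% |
| 0.6 | 4.4% | 4.8% | 6.27% |
| 1.0 | 3.9% | 4.9% | 6.77% |

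If the scale is chosen by its result, the error rate for one comparison is about 6.0 to 6.8% instead of 5%. If the scale is chosen without regard to the result, this inflation does not arise. These rates therefore bound one form of steering under stated assumptions; they do not estimate bias in this trial.

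**The case against.** Several points on the other side are sound.

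- *The article does not say that secondary outcomes are analysed after the break.* A reader might infer that about 40 outcomes are in fact analysed unblinded. The text does not support that. It gives no timing for those analyses, and its description of analysts as blinded is not confined to the primary outcome. Only the weaker statement holds: the protocol permits it.
- *Weight adjustment is not an example.* A reader might count it among the choices left open. It is a conditional rule that must be settled before the primary analysis ends, while the code is closed.
- *A SAP may fix diagnostics and transformations.* It may, and that would close much of the route to bias. Their absence from an article is not the complaint. The time of opening the code is a rule this document states, and it would stand unless amended.
- *The shared A, B and C labels make matters worse.* At a planned break the whole dataset is meant to be opened, so the labels add nothing here.
- *Laboratory work is largely protected.* Much of it uses automated analyzers or commercial kits on samples bearing a participant code, and reading off a treatment would need both the sequence list and the key. This lowers the risk at the assay stage but does not touch the analyst's decisions.
- *The count overstates importance.* Directional biomarker predictions are made for NO and ACE activity only, not for renin or the routine chemistry, and all three hypotheses concern 24-h SBP. This stands, and it limits the weight of the point.

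The Discussion's argument that outcomes are objectively measured answers a different question: whether participants who guess their treatment could alter a reading.

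**Conclusion.** The point holds as a permission that the protocol grants, not as a statement of what will happen. The single planned trigger covers one variable and leaves 40 (41 less body weight) that may be analysed with treatments known, 31 of them from samples that may also be assayed then. The judgement still open is the residual check and transformation, and the outcomes where it matters most are NO and ACE activity.

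The 24-h SBP result, the three hypotheses and the sample size are untouched. The size of any bias cannot be derived from the document; the illustrative error rates rest on assumed data and on a choice steered by the result. The conclusion assumes that no unseen document sets a later time for opening the code. It is a modest improvement worth making because it is cheap.

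**What to change.** In the Blinding section, replace the sentence that sets the time of the code break with:

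> The treatment code will be broken only after the listed laboratory assays are complete, the database is locked, and the prespecified primary and secondary analyses, including model and transformation decisions, have been run by label A, B, C.

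Keep the existing adverse-event exception as it stands.

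No sample size, power, significance level or trial procedure changes. The real cost is time: the unblinded primary result would have to wait for the assays on frozen samples and for the secondary analyses.
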